## Abstract

**Background:**

Ovarian function suppression (OFS) has been shown to be effective as adjuvant endocrine therapy in premenopausal women with hormone receptor-positive breast cancer. However, it is currently unclear if addition of OFS to standard tamoxifen therapy after completion of adjuvant chemotherapy results in a survival benefit. In 2008, the Korean Breast Cancer Society Study Group initiated the ASTRRA randomized phase III trial to evaluate the efficacy of OFS in addition to standard tamoxifen treatment in hormone receptor-positive breast cancer patients who remain or regain premenopausal status after chemotherapy.

**Methods:**

Premenopausal women with estrogen receptor-positive breast cancer treated with definitive surgery were enrolled after completion of neoadjuvant or adjuvant chemotherapy. Ovarian function was assessed at the time of enrollment and every 6 months for 2 years by follicular-stimulating hormone levels and bleeding history. If ovarian function was confirmed as premenopausal status, the patient was randomized to receive 2 years of goserelin plus 5 years of tamoxifen treatment or 5 years of tamoxifen alone. The primary end point will be the comparison of the 5-year disease-free survival rates between the OFS and tamoxifen alone groups. Patient recruitment was finished on March 2014 with the inclusion of a total of 1483 patients. The interim analysis will be performed at the time of the observation of the 187th event.

**Discussion:**

This study will provide evidence of the benefit of OFS plus tamoxifen compared with tamoxifen only in premenopausal patients with estrogen receptor-positive breast cancer treated with chemotherapy.

**Trial registration:**

ClinicalTrials.gov Identifier NCT00912548. Registered May 31 2009. Korean Breast Cancer Society Study Group Register KBCSG005. Registered October 26 2009.

## Background

Many prospective randomized trials have shown that adjuvant endocrine therapy, such as with tamoxifen or ovarian function suppression (OFS), provides a disease free survival benefit for young patients with hormone receptor-positive breast cancer [1–3]. However, there is insufficient information whether adding OFS to standard tamoxifen treatment for premenopausal patients is an effective therapy in reducing disease recurrence.

Premenopausal breast cancer patients with hormone receptor-positive disease have a worse prognosis than postmenopausal breast cancer patients with hormone receptor-positive disease [4, 5]. This difference in survival may be due to tamoxifen resistance in premenopausal women [5]. Theoretically, the combination of OFS and tamoxifen therapy could overcome tamoxifen resistance in premenopausal women. However, in the absence of clinical evidence of a definitive survival benefit associated with OFS plus standard tamoxifen therapy, additional toxicities from OFS treatment complicate recommendation of this treatment regimen. Therefore, it is important to identify patients most likely to benefit from additional OFS treatment.

The results of the Suppression of Ovarian Function Trial (SOFT), a randomized, phase 3 trial conducted by The International Breast Cancer Study Group (IBCSG), showed no significant benefit from the addition of ovarian suppression to tamoxifen in overall patients [6]. However, in women who remained premenopausal and were at sufficient risk of recurrence to warrant adjuvant chemotherapy, the addition of OFS improved disease outcomes. In SOFT, ovarian function was assessed by serum E2 measurement just one time within 8 months after chemotherapy regardless of menstruation. However, it is assumed that examination at only one time point may be insufficient to evaluate ovarian function after chemotherapy. The patients who regain ovarian function later may lose the chance to benefit from the addition of ovarian suppression treatment. The patients who regain ovarian function later may lose their chance to benefit from the addition of ovarian suppression treatment. As there is no standard method to predict the resumption of ovarian function at the time of chemotherapy completion, we decided to evaluate ovarian function repeatedly for 2 years.

The Korean Breast Cancer Society Study Group has designed and initiated a randomized phase III trial comparing OFS plus tamoxifen versus tamoxifen only after chemotherapy in young women with estrogen receptor-positive breast cancer (ASTRRA); participants include those with premenopausal status or those who have regained ovarian function after the completion of neoadjuvant or adjuvant chemotherapy. The primary objective of this study is to compare the 5-year disease-free survival rates between the two groups.

## Methods/design

### Study design and setting

ASTRRA is a phase III open-label, prospective, randomized, multicenter investigator initiated clinical trial. The trial was designed to evaluate the combination of 2 years of goserelin plus 5 years of tamoxifen (OFS group) versus 5 years of tamoxifen alone (tamoxifen alone group) as adjuvant endocrine therapy according to ovarian function after the completion of neoadjuvant or adjuvant chemotherapy in patients with estrogen receptor-positive breast cancer. The Korean Breast Cancer Society Study Group coordinates the trial, and the Steering Committee oversees the trial. The institutional review board of Korea Cancer Center Hospital was approved the protocol version 1.3 [K-0902-004-009]. The study protocol was approved by each institutional review board of all participating centers as well. Table 1 shows the list of participating centers. All patients provided written informed consent before enrollment.

**Table 1 Tab1:** List of participating centers of ASTRRA trial

Names of institutes
Ajou University, School of Medicine
Cheil General Hospital and Women’s Healthcare Center, Dankook University College of Medicine
Chonbuk National University Medical School
Chonnam National University Hwasun Hospital
Chungnam National University Hospital
Chungbuk National University College of Medicine and Medical Research Institute
Daejeon St. Mary’s Hospital, The Catholic University of Korea
Dong-A University Hospital
Eulji University Hospital
Gachon University Gil Hospital
Gangnam Severance Hospital, Yonsei University
Hallym University Sacred Heart Hospital, College of Medicine, Hallym University
Inha University Hospital, Inha University
Inje University Busan Paik Hospital
Inje University Sanggye Paik Hospital, Inje University College of Medicine
KangDong sacred heart hospital, Hallym university
Kangseo Mizmedi Hospital
Keimyung University School of Medicine
Konkuk University School of Medicine
Korea Cancer Center Hospital, Korea Institute of Radiological and Medical Sciences
Korea University Anam Hospital
Mokdong Hospital, Ewha Womans University
Myongji Hospital
National Cancer Center
Samsung Medical Center, Sungkyunkwan University School of medicine
Seoul National University Boramae Medical Center
Seoul National University Hospital, Seoul National University College of Medicine
Seoul St. Mary’s Hospital, Medical College of The Catholic University of Korea
Soonchunhyang University College of Medicine, Cheonan Hospital
Soonchunhyang University Colleage of Medicine
Soonchunhyang University College of Medicine, Bucheon Hospital
Sungkyunkwan University School of Medicine, Kangbuk Samsung Hospital
University of Ulsan, Asan Medical Center
Yeungnam University Hospital
Yonsei University College of Medicine

**Table 2 Tab2:** Demographics of randomized patients

	Tamoxifen only group (B + D group, *N* = 655)	Ovarian function suppression group (C + E group, *N* = 634)	*P*-value
Age(mean, years)	39.7 ± 4.1	39.6 ± 4.1	0.580
Stage			
I	178 (27.2 %)	169 (26.7 %)	0.977
II	335 (51.1 %)	332 (52.4 %)	
III	121 (18.5 %)	113 (17.8 %)	
Unidentified	21 (3.2 %)	20 (3.2 %)	
Lymph node status			
Negative	279 (42.6 %)	275 (43.4 %)	0.927
Positive	371 (56.6 %)	355 (56.0 %)	
Unidentified	5 (0.8 %)	4 (0.6 %)	
Histology			
Invasive ductal carcinoma	573 (87.5 %)	560 (88.3 %)	0.917
Invasive lobular carcinoma	32 (4.9 %)	26 (4.1 %)	
Others	42 (6.4 %)	41 (6.5 %)	
Unidentified	8 (1.2 %)	7 (1.1 %)	
Histologic grade			
G1	95(14.5 %)	118 (18.6 %)	0.229
G2	359 (54.8 %)	323 (50.9 %)	
G3	160 (24.4 %)	151 (23.8 %)	
Unidentified	41(6.3 %)	42 (6.6 %)	
Chemotherapy regimen			
Anthracycline + cyclophosphamide	184 (28.1 %)	185 (29.2 %)	0.782
Anthracycline + cyclophosphamide followed by taxane	324 (49.5 %)	318 (50.2 %)	
Anthracycline + taxane	30 (4.6 %)	29 (4.6 %)	
5-fluorouracil + anthracycline + cyclophosphamide	74 (11.3 %)	73(11.5 %)	
Others	21 (3.2 %)	14(2.2 %)	
Unidentified	22 (3.4 %)	15 (2.4 %)	
Operation			
Total mastectomy	268 (40.9 %)	248 (39.1 %)	0.762
Breast conserving surgery	382 (58.3 %)	382 (60.3 %)	
Unidentified	5 (0.8 %)	4 (0.6 %)	

### Patients

The trial enrolled premenopausal women ≤ 45 years of age with histologically confirmed estrogen receptor-positive, stage I–III, primary invasive breast cancer treated with definitive surgery and chemotherapy. Premenopausal status for inclusion criteria was defined as having a regular menstruation history at the time of diagnosis. Estrogen receptor positivity was determined as expression of estrogen receptor in at least 10 % of tumor cells as determined by immunohistochemistry or 10 fmol/mg cytosol protein as determined by a dextran-coated charcoal ligand binding assay.

Receipt of neoadjuvant or adjuvant chemotherapy was required, and the standard regimens were allowed except CMF. Adjuvant trastuzumab therapy for patients with human epidermal growth factor receptor-2-positive disease was permitted, although it was not considered as chemotherapy.

We excluded patients with other primary malignancies within the last 5 years, except for adequately treated in situ carcinoma of the cervix, basal cell carcinoma, or squamous cell carcinoma of the skin. In addition, patients with thrombocytopenia, those currently treated with anti-coagulant agents, and patients that were pregnant, lactating, or treated with investigational drugs within the previous 4 weeks before baseline assessment were excluded.

### Study design

The first screening test to evaluate ovarian function was performed within 3 months of the final dose of chemotherapy. Premenopausal status at the first screening test was defined by serum follicular stimulating hormone (FSH) levels < 30 mIU/ml. At 6, 12, 18, and 24 months following the baseline assessment, ovarian function status is to be evaluated by menstruation status and serum FSH levels. Regaining premenopausal status is defined by FSH levels < 30mIU/ml or bleeding history within 6 months of each visit. Study visits will be every 6 months for 5 years and at least yearly thereafter, according to each institute’s routine practice. If the patient does not regain satisfy the definition of being premenopausal during the 24 months after enrollment, the patient will be categorized to the permanent menopause group (group A). At each visit, newly confirmed premenopausal patients will be randomly assigned in a 1:1 ratio to the OFS group (group C or group E) or the tamoxifen alone group (group B or group D). The OFS group is treated with 3.6 mg subcutaneous injection goserelin (Zoladex® [D-Ser(But)^6^ Azgly^10^ luteinizing-hormone-releasing hormone]; AstraZeneca) every 28 days for 2 years plus oral tamoxifen at a dose of 20 mg daily for 5 years. The tamoxifen only group is treated with oral tamoxifen at a dose of 20 mg daily for 5 years. Randomization is performed by means of an internet-based system and is stratified according to lymph node status (negative versus positive) and institutes (Fig. 1). Data are collected and stored in a digital case report form.

**Fig. 1 Fig1:**
[figure not shown]
Study design

### Primary and secondary end points

The primary end point is to compare the 5-year disease-free survival rates between the OFS and tamoxifen alone groups, particularly among patients with premenopausal status (assessed every 6 months for 2 years) after the completion of chemotherapy. Disease-free survival is defined as the time from enrollment to the detection of invasive recurrence of breast cancer (local, regional, or distant metastasis), contralateral breast cancer, secondary malignancy, or death without breast cancer recurrence. Patients who are still alive without any event at the time of the analysis will be censored.

Secondary end points are (1) to compare overall survival rates between groups, (2) to compare 5-year disease-free survival rates between postmenopausal patients treated with tamoxifen and premenopausal patients treated with OFS plus tamoxifen, (3) to determine the tolerability of tamoxifen with or without goserelin.

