### Sample size calculation and statistics

Planned enrollment was at least 1234 patients. Initially, the design projected that 2 years of accrual, plus 5 years of additional follow-up would be sufficient to observe the target of 374 disease-free survival events across the two treatment arms, with 85 % power to detect 7 % reduction in hazard with OFS plus tamoxifen versus tamoxifen alone. In 2010, because of a slower-than-expected enrollment rate, the steering committee extended the accrual period from 2 years to 4 years.

An intent-to-treatment analysis and per-protocol analysis will be performed. The disease-free survival rate will be evaluated using the Kaplan-Meier method. The log-rank test will be used to compare the treatment groups. Multivariate analyses will be performed using Cox’s proportional hazards model.

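### The named primary comparison is the 5-year DFS rate, but the test, event target, power statement and interim trigger belong to an event-driven log-rank comparison, so the 85 % power is not shown to hold for the end point as worded

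*Protocol article*

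**What the plan says.** Under Primary and secondary end points, the article says: "The primary end point is to compare the 5-year disease-free survival rates between the OFS and tamoxifen alone groups". The same section gives the underlying variable as a time: "Disease-free survival is defined as the time from enrollment to the detection of invasive recurrence of breast cancer", with further event types listed after it. It adds: "Patients who are still alive without any event at the time of the analysis will be censored". No truncation at 5 years is mentioned.

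Under Sample size calculation and statistics, the rate is to be estimated ("The disease-free survival rate will be evaluated using the Kaplan-Meier method") and the groups tested ("The log-rank test will be used to compare the treatment groups"). The design rests on 374 DFS events in the two arms together, and the power statement attached to that number reads: "with 85 % power to detect 7 % reduction in hazard with OFS plus tamoxifen versus tamoxifen alone". At least 1,234 patients were planned, with 2 years of accrual and 5 more of follow-up; accrual was later extended to 4 years. Trial progress places the first interim at 187 events, half of 374.

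No test of the difference at 5 years is named. Alpha and the assumed 5-year rates are not given.

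**The concern.** A comparison of 5-year rates is a contrast of two survival curves at one time point. A log-rank test compares hazards over all the follow-up that enters it. The two agree closely when hazards are proportional, but they are different targets with different power.

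Two features make the difference relevant here. First, the Study design section continues visits at least yearly after year 5, and censoring is at the time of analysis. Later events therefore enter the log-rank test, but they cannot change a 5-year rate. Second, goserelin is given for 2 years and tamoxifen for 5, so a constant hazard ratio up to and beyond year 5 cannot be taken for granted.

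What is at stake is whether the primary test answers the question the end point names, and whether the quoted power belongs to it.

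**Working it through.** **Inputs from the article:** 374 events, 85 % power, 1,234 patients (617 per arm, 1:1), 2 + 5 years, accrual later 4 years; actual recruitment March 2009 to March 2014 (5 years), with 634 + 655 = 1,289 randomized by January 2015.

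**Assumptions, not in the article:** two-sided alpha 0.05, exponential hazards, uniform accrual, no dropout, and time counted from entry with no delay between enrollment and randomization. The 5-year rates are varied.

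**Step 1. The plan's own figure, read literally.** Log-rank power (Schoenfeld) = Φ(√D·|ln HR|/2 − 1.96). With HR = 0.93 and D = 374: √374 × 0.0726/2 = 0.70, and Φ(0.70 − 1.96) = 10.4 % (17.3 % one-sided). Events needed for 85 %: 4(1.960 + 1.036)²/0.0726² ≈ 6,820. The stated 85 % does not reproduce for a 7 % relative reduction in hazard.

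**Step 2. What the 374 events fit.** Turning the formula round, 374 events give 85 % at HR = exp(−2 × 2.996/√374) = 0.734. A 7-point absolute gain from 70 % to 77 % gives HR = ln 0.77/ln 0.70 = 0.733, for which:
- 372 events are needed (Schoenfeld) or 378 (Freedman);
- log-rank power at 374 events is Φ(3.006 − 1.96) = 85.2 %;
- about 380 events are expected in 1,234 patients over 2 + 5 years.

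These rates fit the event target, the sample size and the timetable together.

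**Step 3. Power of a fixed 5-year comparison under 70 % vs 77 %.** Power = Φ(0.07/SE − 1.96), with SE from the Greenwood variance of each Kaplan-Meier estimate at 5 years and the analysis taken when 374 events are reached.

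| N, accrual | Analysis time | SE | Power, difference | Power, log-log scale | Events after year 5 |
|---|---|---|---|---|---|
| 1,234, 2 years | 6.88 y | 0.0251 | 79.8 % | 79.2 % | 12.6 % |
| 1,234, 4 years | 7.91 y | 0.0256 | 78.2 % | 77.6 % | 14.8 % |
| 1,289, 5 years | 8.13 y | 0.0258 | 77.5 % | 77.0 % | 14.3 % |

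First row: 0.07/0.0251 = 2.79, and Φ(2.79 − 1.96) ≈ 80 %.

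**Step 4. Sensitivity to the assumed rates.** With the same 7-point gap, 617 per arm and everyone followed to 5 years, fixed-time power by the two-proportion formula is:
- 60 % vs 67 %: 72 %
- 65 % vs 72 %: 76 %
- 70 % vs 77 %: 80 %
- 75 % vs 82 %: 85 %
- 80 % vs 87 %: 91 %

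At 75 % vs 82 % the formula needs exactly 617 per arm, that is 1,234. But those rates fit the event target poorly: only about 311 events would be expected in 2 + 5 years, and 374 events would give 95 % log-rank power. Reaching 374 would also put 26-29 % of events after year 5.

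**The case against.** The strongest reply is that the 5-year rate is shorthand. The article defines DFS as a time, censors at analysis, uses Kaplan-Meier for the rate and the log-rank for the comparison; read together, this is an ordinary time-to-event design. That reading is plausible, and it is the one the fix adopts. But it has to be inferred against the wording of the primary end point, and that a log-rank test runs over all follow-up is itself inferred from the censoring rule.

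Second, if the design effect was 70 % to 77 %, it was set on the 5-year scale and converted to a hazard ratio, so end point and power are linked. That stands, and it limits the gap to roughly 5-8 points under those rates. Part of that gap comes from analysing at 374 events before everyone reaches 5 years: with 1,289 patients, 5-year accrual and a full 5 years of further follow-up, fixed-time power is 81.5 %. Nor is 1,289 final, since 114 patients were still being evaluated.

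Third, non-proportional hazards are a possibility raised by the treatment durations, not something the document shows. That also stands.

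A reader might further infer that the plan lacks a rule for choosing between two conflicting primary results. The document does not support this: only one between-group test is named, so there is no second test to conflict with it, and such a hierarchy could sit in an analysis plan that is not shown.

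**Conclusion.** The mismatch is in the text. The end point is worded as a fixed-time rate, while the test, event target, power statement and interim trigger are those of an event-driven DFS comparison. Under 70 % vs 77 %, about 13-15 % of the 374 events would fall after year 5 and influence the test without bearing on the stated end point.

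The power consequence is conditional. A reader might infer that the 85 % is simply wrong for the 5-year comparison, or that it is a sound log-rank figure that fails to carry over. Neither is supported. The first depends on rates the article does not give: about 77-80 % under the best-fitting rates, about 85 % at 75 % vs 82 %. The second fails because, with the effect as written, the log-rank itself has only about 10 % power. What can be said is that the 85 % is not shown to hold for the end point as worded. All figures assume two-sided 0.05, exponential hazards, uniform accrual and no dropout.

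**What to change.** Name one primary comparison, before any unblinded result is seen. Either:

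- **Preferred:** state the primary end point as DFS (time to event), compared by the log-rank test at the planned event number and summarised by a hazard ratio, with the 5-year Kaplan-Meier rates and their difference with 95 % CI as a supporting summary; or
- keep the 5-year rate as primary, test the Kaplan-Meier difference at 5 years, and restate the power for that test.

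In both cases state alpha, the assumed 5-year rates and the hazard ratio that lead to 374 events and 1,234 patients, and correct the effect-size wording if an absolute 7-point difference was meant.

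The first option is a change of wording and needs no extra patients. The second needs a new power statement; under 70 % vs 77 %, holding 85 % with complete 5-year follow-up would take 713 per arm (1,426 in all). The time origin (enrollment or randomization) and stratification of the test are separate points and are not part of this change.

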### Trial progress

Recruitment was closed on March 2014. Between March 2009 and March 2014, 1485 patients were screened, and 1483 patients from 35 institutes in South Korea were enrolled in this study. On January 12 2015, 634 patients were randomized to the OFS group, and 655 patients were randomized to the tamoxifen only group (Table 2). Eighty patients were classified as permanent menopause status. Another 114 patients continue to exhibit a status of chemotherapy-induced amenorrhea, and the ovarian function of these patients is being evaluated every 6 months. All of the patients received chemotherapy before randomization. Node-positive disease was present in 56.3 % of the patients. The first interim analysis will be performed when 50 % of the planned disease-free survival events (187 events) have occurred.

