The proportion of patients with regained ovarian function is slightly higher in the ASTRRA trial than in other reports. This might be caused by the exclusion of patients treated with CMF regimens [16, 17]. Because most patients treated with CMF do not recover from chemotherapy-induced amenorrhea, we excluded patients who had received the CMF regimen [8, 16, 17]. In contrast to the CMF regimen, modern non-CMF chemotherapy regimens result in less permanent amenorrhea after treatment. The NSABP B-30 trial assessed menstrual status after various non-CMF chemotherapy regimens at baseline and every 6 months over 24 months. The incidence of amenorrhea 12 months after random assignment was 69.8 % for sequential doxorubicin and cyclophosphamide followed by docetaxel, 57.7 % for concurrent docetaxel-doxorubicin-cyclophosphamide, and 37.9 % for concurrent docetaxel-doxorubicin (*P* < 0.001) [18]. Although CMF is an effective chemotherapy regimen for breast cancer patients, use of the CMF regimen in young patients is currently decreasing in South Korea. Thus, we believe that the removal of the CMF regimen from the trial’s acceptable chemotherapy regimen list is compatible with recent trends in the care of young women with breast cancer. Another reason for the high rate of ovarian function resumption in the ASTRRA trial would be the relatively young age of participants. The NSABP B-30 trial showed that age is significantly related to the incidence of chemotherapy-induced amenorrhea [18].

The important advantage of the ASTRRA trial study design is the repeated evaluation of ovarian function. The longitudinal evaluation of ovarian function may help to select the most appropriate patients to receive additional OFS treatment, thereby avoiding unnecessary side effects. OFS causes menopausal symptoms and bone mass loss [19, 20]; menopausal symptoms, such as vasomotor symptoms, vaginal dryness, vaginal discharge, anxiety, depression, or sleep disturbances, significantly affect quality of life [19]. Sometimes these symptoms result in low compliance or destroy the physician-patient relationship. Because there is yet no reliable biomarker to select patients most likely to benefit from OFS, continuous checking of ovarian function may facilitate this patient selection.

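### Secondary end point 2 compares a small, non-randomized menopausal group with the randomized OFS arm, and no adjusted analysis is tied to it, so neither a difference nor similarity can be read without regard to patient mix

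*Protocol article*

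**What the plan says.** The second secondary end point (Primary and secondary end points) is "to compare 5-year disease-free survival rates between postmenopausal patients treated with tamoxifen and premenopausal patients treated with OFS plus tamoxifen".

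The Study design section explains how the groups arise. At each visit, "newly confirmed premenopausal patients will be randomly assigned in a 1:1 ratio" to OFS or to tamoxifen alone. For a woman who does not meet the premenopausal definition within 24 months of enrollment, "the patient will be categorized to the permanent menopause group (group A"). Group A is the only postmenopausal group described, so it must be the comparator. The article does not link the two explicitly and does not state group A's treatment.

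Trial progress gives the numbers at January 2015: "Eighty patients were classified as permanent menopause status", and "Another 114 patients continue to exhibit a status of chemotherapy-induced amenorrhea". The OFS arm has 634 women.

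Under Sample size calculation and statistics, disease-free survival rates are evaluated by Kaplan-Meier and "The log-rank test will be used to compare the treatment groups". Multivariable Cox models are also planned, but the article does not say for which comparison or with which covariates.

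On who loses ovarian function, the Discussion reports from a cited trial that "age is significantly related to the incidence of chemotherapy-induced amenorrhea". From the same trial it gives amenorrhea at 12 months of "69.8 % for sequential doxorubicin and cyclophosphamide followed by docetaxel, 57.7 % for concurrent docetaxel-doxorubicin-cyclophosphamide, and 37.9 % for concurrent docetaxel-doxorubicin". It also offers the youth of this trial's participants as one reason why so many regained ovarian function.

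**The concern.** The two groups in this end point differ in more than treatment. The OFS arm was formed by randomizing women with functioning ovaries. Group A was formed by how each woman's ovaries responded to chemotherapy. By the article's own account that response is related to age and varies with regimen. If either also bears on recurrence, the two 5-year rates will differ, or coincide, for reasons unrelated to endocrine therapy.

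Two misreadings are at stake. Similar rates could be taken to mean that OFS brings premenopausal women to the outcome of menopausal women. Lower disease-free survival on OFS could be taken to mean that OFS falls short. The small size of group A makes the first misreading more likely, because a log-rank test with few events will often be non-significant whatever the truth.

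**Working it through.** The plan states no design calculation for this end point. The 374 events and 85 % power concern the two randomized arms, so there is no planned figure to reproduce. The patient counts do reconcile: 634 + 655 + 80 + 114 = 1483.

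**Direction of selection.** The Discussion attributes the high recovery rate partly to young age, so group A should be older than the randomized women. All participants are at most 45, which limits the gap. For regimen, the 12-month figures show that amenorrhea can vary widely between regimens without CMF. They do not show which of this trial's regimens feed group A.

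**Precision: inputs.**
- OFS arm: 634 (Trial progress).
- Group A: 80 now, and at most 80 + 114 = 194 if no pending woman regains function.
- 5-year disease-free survival, taken as equal in both groups: an assumption, since the article gives none. I use 85 % and 70 %. The latter is close to the design's own ratio, 374 / 1234 = 30.3 % with an event.

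**Formulas.**
- Events = n × (1 − S).
- SE(log HR) = √(1/e_A + 1/e_OFS).
- 95 % factor = exp(1.96 × SE).
- Half-width of the 95 % interval for the rate difference, with complete follow-up = 1.96 × √[S(1 − S)(1/n_A + 1/634)].
- Power for HR 0.75, two-sided 5 % (assumed) = Φ(0.288/SE − 1.96).

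| S | n_A | e_A | e_OFS | SE | HR × or ÷ | Rate difference ± | Power, HR 0.75 |
|---|---|---|---|---|---|---|---|
| 85 % | 80 | 12 | 95 | 0.306 | 1.82 | 8.3 points | 15 % |
| 85 % | 194 | 29 | 95 | 0.212 | 1.51 | 5.7 points | 27 % |
| 70 % | 80 | 24 | 190 | 0.217 | 1.53 | 10.7 points | 26 % |
| 70 % | 194 | 58 | 190 | 0.150 | 1.34 | 7.4 points | 48 % |

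In every row a true hazard ratio of 0.75 would more often than not give a non-significant test.

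**Illustration of patient mix.** Suppose a factor is present in a share p of group A and in half of the OFS arm, and multiplies the hazard by r. With no treatment effect, the crude hazard ratio is approximately (1 + (r − 1)p) / (1 + (r − 1) × 0.5).
- r = 1.5, p = 0.6: 1.30 / 1.25 = 1.04.
- r = 2, p = 0.8: 1.80 / 1.50 = 1.20.

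Only the one-half has a source: 318 of 634 OFS women had the sequential taxane regimen (Table 2). The values of r and p are assumed, so this shows the mechanism and is not an estimate of the bias.

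**The case against.** The strongest reply is that the article claims little for this comparison. It says only that two rates will be compared. It makes no equivalence claim, and neither of the two questions that the Discussion says the trial was started to answer is this one. The effect of OFS is carried by the randomized primary comparison. A benchmark against permanently menopausal women is a legitimate secondary aim, and adjustment may be specified in the full protocol or analysis plan. This stands in part. The article does not rule out an adjusted analysis. But it fixes the two groups and the 5-year rate as the measure, and its general Cox sentence is not tied to this end point.

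Four stronger readings are tempting, and the text does not support them:

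- A reader might infer that age and regimen determine who becomes menopausal. The Discussion says only that age is related. Its regimen percentages are amenorrhea at 12 months in another trial, not permanent menopause.
- A reader might infer that group A must be richer in sequential taxane treatment. The article gives no amenorrhea figure for the non-taxane regimens, which were used in 29.2 % and 11.5 % of the OFS arm. The lowest figure, 37.9 %, belongs to a type of regimen used in only 4.6 %.
- A reader might infer that the end point is meant to show what OFS achieves. No passage says so.
- A reader might infer that leaving out the tamoxifen-alone arm loses essential information. In a single Cox model, the gap between group A versus tamoxifen alone and group A versus OFS is the randomized OFS effect, which the primary comparison already supplies.

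It is also true that the largest illustrative shift, 1.20, is smaller than the random error in every row of the table. With so few events, imprecision is at least as serious as confounding.

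**Conclusion.** The point holds as a limit on what secondary end point 2 can show. It is not a contradiction or a numerical error in the article. The comparator is not randomized, the article itself links age and regimen to amenorrhea, and no adjusted analysis is attached to the comparison. A crude result in either direction may reflect who is in group A.

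The imprecision is the part that can be sized. The 95 % interval is the hazard ratio times or divided by about 1.8 to 1.5 at 85 % disease-free survival, and about 1.5 to 1.35 at 70 %. Both survival figures are assumptions, and group A's final size lies somewhere between 80 and 194. The size and direction of the confounding cannot be derived from the document, which gives neither group A's characteristics nor the prognostic effect of age or regimen.

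A separate problem affects the same contrast. Group A is known only at 24 months, yet disease-free survival runs from enrollment. If membership requires being event-free until then (assumption) and the hazard is constant, a true 5-year rate S would appear as S^(3/5): 70 %, 80 % and 90 % would appear as about 81 %, 87.5 % and 94 %. Covariate adjustment does not remove this.

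**What to change.** In the section on end points, or in the analysis plan:

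1. Identify the postmenopausal group as group A, and label secondary end point 2 a non-randomized, descriptive comparison.
2. Make its main analysis a Cox model, or an adjusted difference in 5-year disease-free survival, with age, stage, nodal status, grade and chemotherapy regimen as covariates. All five are tabulated for the randomized women in Table 2.
3. Report the estimate with a 95 % confidence interval, and state that a non-significant test will not be taken as evidence of similarity.
4. State that adjustment reduces confounding but does not remove it.
5. Handle the 24-month classification separately, for example with a landmark at 24 months.
6. Optionally, show group A versus tamoxifen alone from the same model, for context only.

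The cost is the wording of one secondary end point and an analysis that should need no new data. With only 12 to 29 group A events at 85 % disease-free survival, the covariates should be coded sparingly. If the Cox model is chosen, a hazard ratio replaces the crude rate difference, and that change of measure should be stated. A landmark drops events before 24 months from this comparison. The conclusion will be more cautious.
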